##### Psychiatric hospitalizations and emergency department use

Medicaid claims data will be used to measure psychiatric hospitalizations and emergency department use identified by relevant ICD-9-CM diagnostic codes (290 through 314), CPT codes, place of service and revenue center codes. The occurrence of any psychiatric hospitalization, the number of hospitalizations and the length of stay for each will be coded.

##### Employment, housing and forensic involvement status

This information will be extracted from the state Annual Consumer Reporting Form, which contains questions about (1) primary employment, secondary employment and hours worked per week during the past 90 days; (2) residence and whether the consumer has been homeless in the past 30 days; and (3) current legal involvement.

##### Consumer satisfaction with services, social connectedness and improved functioning

These domains will be measured by using state data from the Consumer/Client Satisfaction Survey, which consists of the state version of the Mental Health Statistics Improvement Program Consumer Survey, version 1.2 [46]. This 43-item measure has 23 items that measure consumer satisfaction with services, 13 items that measure functioning, and 4 items that measure social connectedness. Higher scores reflect greater satisfaction, functioning and connectedness.

#### Consumer demographic and clinical characteristics

Consumer diagnosis, comorbid medical and substance abuse diagnoses, sex, age and race will be obtained from the Medicaid claims data for inclusion as covariates in our models.

### Quantitative Data analysis

All analyses will be done by intent to treat (ITT). Differences across the two arms of the study (PCCP and treatment as usual) will be analyzed using the PROC MIXED statement in SAS statistical software (SAS Institute, Cary, NC, USA) to create mixed-effects multivariate regression models. Mixed-effects models will permit the appropriate analysis of nesting of study subjects within sites and repeated measurement of outcomes for subjects over time. Descriptive statistics will be examined for treatment groups and for additional groups as needed (for example, treatment completers versus dropouts). In addition, individual and average trajectories will be plotted for all repeated measures over time according to assigned treatment.

Bivariate analyses will be conducted using *χ*^2^ tests for categorical variables and *t*-tests for continuous dependent variables at each time point to evaluate the differential impact of the PCCP intervention on each consumer and implementation outcome. All models will control for, as fixed effects, baseline consumer factors as appropriate (diagnosis, comorbid medical and substance abuse diagnoses, sex, age, race and psychiatric hospitalization rates). Models will be conducted separately for outcomes from leadership staff, clinical supervisors, chart reviews, state mental health data and Medicaid claims. The unit of observation in all models will be, as appropriate, clinical supervisors, organizational leaders or consumers.

In the analyses for aim 1, we will assess the effectiveness of PCCP on service engagement and clinical outcomes. We will use each outcome as the dependent variable and a dichotomized measure of the PCCP intervention (any intervention versus no intervention) as our independent variable. Controlling for relevant baseline characteristics and including a fixed effect for state, we will use separate mixed linear regression models to determine the impact of the intervention on each of the outcomes at each time point. The primary ITT test and estimation will be done at the 24-month time point with tests at earlier time points. We will then conduct a growth curve analysis with repeated observations representing measures at baseline, 12 months and 24 months. The analysis will include variables for time, treatment and their interaction, but it will be focused on the magnitude and statistical significance of the time × treatment interaction to quantify the relative difference in the rate of outcome change between the treatment groups. All models will include random intercepts and slopes for CMHC and state. We will repeat these analyses to compare each intervention arm to treatment as usual.

The analyses for aim 2 are limited to only clinicians and consumers in agencies exposed to the intervention. Within this population, we will use linear mixed-effects regression models to determine the extent to which clinician assessments of organizational factors, including transformational leadership, recovery orientation and organizational readiness (independent variables), are associated with our primary implementation outcome, which is clinician PCCP competency (dependent variable). Competency will be measured as change from baseline to 12 and 24 months and examined separately at each time point. Our first model will include one observation per clinician and will include a random intercept for organization, but no independent variables. This will allow us to calculate the maximum proportion of variance attributable to the organization (that is, the ICC). A second model will also include our three independent variables as fixed effects. This model will allow us to examine the individual contribution of each organizational factor to explaining competency and also to understand how much of the total explainable organizational variation in our dependent variable from the first model is explained by the three organizational factors in this model. In subsequent models, we will use these same techniques to assess the impact of organizational factors on patient outcomes, including consumer satisfaction with services, service engagement and adherence and consumer clinical and functional status.

Aim 3 is to use qualitative methods to understand how care planning impacts service engagement and how implementation processes influence organization and provider level behavior.

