### Participants

We randomly selected 14 research sites from among all community mental health clinics (CMHCs) in Delaware and Connecticut. These agencies serve approximately 8,000 consumers. We used the Power and Precision software package (Biostat, Englewood, NJ, USA) to calculate sample sizes needed to achieve 80% power (α = 0.05) to detect these effects in our two-level hierarchical design where clinicians and patients are nested within CMHCs. The software accounts for this nesting using the intracluster correlation coefficient (ICC), a measure of the relatedness of clustered data that compares the variance within and between clusters. The ICC in our pilot data was 0.013. To achieve the study aims, we will need 280 participants (20 per site). We will need 1,125 medical record reviews (75 per site).

The services delivered at the CMHCs include psychiatric crisis intervention, individual and group therapy, psychiatric evaluation, medication management, case management, community support programs and rehabilitation services. A total of 280 providers will be recruited for the study. Within each research site, five clinical supervisors, ten direct care staff and five leadership staff will be recruited to participate in the study. The supervisors are clinical staff who are directly responsible for supervising the direct care staff. Direct care staff are clinicians who provide frontline services to consumers without any supervisory duties. The supervisors and direct care staff work in the outpatient mental health programs listed above. They come from a variety of disciplines, including social work, psychology, psychiatric rehabilitation, counseling and peer support. The leadership staff are in administrative positions and do not directly supervise direct care staff. Their titles include executive director, medical director, administration direction, operations director, quality improvement director, clinical services directors, peer support or consumer affairs director, training and staff development director, rehabilitation services director, human resources director, and representatives from the agency’s consumer advisory council.

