Each supervisor will nominate two direct care staff who report to them. They will nominate individuals based on whether they fulfill the criteria of change agents, which are that they have worked at the agency for more than 1 year, have demonstrated leadership potential, are open to change and adoption of new practices and are perceived as a resource and/or role model by other direct care staff.

Secondary data will be used to assess consumer outcomes. Consumers eligible for this study will be adults who have received services at the CMHCs continuously for 1 year prior to the study. We will use the Medicaid and state mental health data of all eligible consumers.

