### Randomization

The 14 sites (8 in Connecticut and 6 in Delaware) selected for the study will be randomized into the 2 study arms, yielding 7 sites per condition, balanced by state. A research team member will use SAS 9.3 software to generate the allocation sequence assigning sites to condition. The software will generate randomized lists blocked by state, ensuring three experimental sites and three control sites in Delaware and four experimental sites and four control sites in Connecticut. The responsible team member will be blinded to site-specific information during randomization. Blinding is not possible, given the circumstances of the intervention.

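### Supplementary chi-square and t-tests of the intervention effect ignore randomisation by site; at consumer level a nominal 5% test could have a true size of up to about 50%

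*Protocol article*

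**What the plan says.** The Randomization section states that the 14 sites "selected for the study will be randomized into the 2 study arms, yielding 7 sites per condition, balanced by state". The Participants section (quantitative aims) describes a "two-level hierarchical design where clinicians and patients are nested within CMHCs" and reports: "The ICC in our pilot data was 0.013". Clustering is therefore recognised at the design stage.

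The Quantitative Data analysis section opens with mixed-effects models in PROC MIXED for differences between the arms, justified by the nesting of subjects within sites. Its next paragraph adds bivariate analyses: chi-square where the variable is categorical, and t-tests whose stated scope is "for continuous dependent variables at each time point to evaluate the differential impact of the PCCP intervention on each consumer and implementation outcome". It mentions no adjustment for site.

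The aim 1 paragraph of the same section then returns to mixed linear regression for each outcome at each time point, with random intercepts and slopes for CMHC. The primary intent-to-treat test at 24 months is placed there.

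On the number of consumers, the Participants section says: "These agencies serve approximately 8,000 consumers". It also restricts the analysed group: "Consumers eligible for this study will be adults who have received services at the CMHCs continuously for 1 year prior to the study". The number who meet that condition is not given.

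**The concern.** An ordinary chi-square or t-test treats every consumer, chart or staff member as an independent observation. When whole sites are allocated, people in the same site share an allocation and tend to resemble each other. The standard error of the arm difference is then too small by the square root of the design effect, and the test rejects too often when there is no effect.

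This is a stated rule, not a detail left to an analysis plan. Descriptive statistics are dealt with separately in the preceding paragraph, and the bivariate tests are given the task of judging the intervention's effect. The abstract gives the mixed models that same task. Two methods, one of which ignores the clustering, thus serve one purpose, and no rule says which governs if they disagree.

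The practical risk is that false-positive bivariate results, spread over many outcomes and several time points, are reported as evidence of effect. It is sharpest for categorical consumer outcomes such as no-shows, any psychiatric hospitalisation or homelessness. The article's models are linear, and chi-square is the only method it names specifically for categorical data.

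**Working it through.** The plan states no false-positive rate for these tests, so there is no figure of that kind to reproduce. Its sample size cannot be re-derived either, because no effect size is given. The inputs below come from the article unless marked as assumed.

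**Inputs**
- 14 sites, 7 per arm (Randomization).
- About 8,000 consumers served (Participants). With equal sites this is 8,000 / 14 = 571.4 per site, an upper bound on the average eligible number per site.
- 75 charts per site and 20 staff per site, including 5 supervisors and 5 leaders (Participants).
- ICC 0.013 (Participants). The outcome it refers to is not stated, so using it for consumer outcomes is an assumption.
- Alpha 0.05 (Participants), assumed two-sided.
- Assumed for the range: half, a quarter or a tenth of consumers eligible; ICC 0.005 and 0.05 as alternatives.

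**Formulae**, with m the number analysed per site:
- Design effect: DE = 1 + (m − 1) × ICC.
- True size of an unadjusted nominal 5% test: 2 × [1 − Φ(1.96 / √DE)].

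**Worked case**, all consumers analysed: DE = 1 + 570.4 × 0.013 = 8.42; √DE = 2.90; 1.96 / 2.90 = 0.68; size = 49.9%.

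**Results at ICC 0.013**

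| Data | m per site | DE | True size |
|---|---|---|---|
| Consumers, all 8,000 | 571.4 | 8.42 | 49.9% |
| Consumers, half | 285.7 | 4.70 | 36.6% |
| Consumers, a quarter | 142.9 | 2.84 | 24.5% |
| Consumers, a tenth | 57.1 | 1.73 | 13.6% |
| Charts | 75 | 1.96 | 16.2% |
| All staff | 20 | 1.25 | 7.9% |
| Supervisors or leaders alone | 5 | 1.05 | 5.6% |

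**Sensitivity to the ICC at 571.4 per site**
- ICC 0.005: DE = 1 + 570.4 × 0.005 = 3.85, size 31.8%.
- ICC 0.05: DE = 1 + 570.4 × 0.05 = 29.52, size 71.8%.

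**Unequal site sizes.** Replacing m by (1 + CV²) × m, with an assumed coefficient of variation of 0.4 to 0.65, raises 49.9% to 52.7-56.4%.

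**Simulation check** (pooled t-test, 7 v 7 sites, ICC 0.013, 20,000 runs): 49.9% at 571 per site, 36.4% at 286, 16.3% at 75 and 7.8% at 20, in line with the formula. A t-test on the 14 site means with 12 degrees of freedom rejected in 5.1% of runs, which is nominal.

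**Allocations available to a permutation test.** Blocking by state gives C(8,4) × C(6,3) = 70 × 20 = 1,400. The smallest attainable two-sided p-value is 2 / 1,400 = 0.0014.

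**The case against.** The strongest reply is that the plan's main analysis already handles clustering. The section opens with mixed models chosen for the nesting within sites. The aim 1 paragraph assigns each outcome at each time point to such a model, and the primary 24-month test sits there. That stands. A reader might infer from the bivariate sentence that the arms are compared only by tests that ignore site, or that the trial's primary conclusion carries a false-positive rate near 50%. The article supports neither reading: the chi-square and t-tests are an addition.

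The reply also holds on size. The 50% figure needs all consumers served to be analysed, although eligibility requires a year of continuous service. Some outcomes come from Medicaid claims or a satisfaction survey, whose coverage is not stated. The ICC is borrowed from an unnamed pilot outcome. If the bivariate tests follow the article's separate modelling of leaders and supervisors, five of each per site, the inflation for those groups is negligible (5.6%).

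None of this makes the added tests valid. Even with a tenth of consumers eligible, the size at the plan's ICC is nearly three times nominal. The text does not call the tests descriptive or rank them below the models.

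**Conclusion.** The point holds as a defect in a supplementary analysis. The article prescribes unadjusted tests of the intervention effect in a trial that randomises 14 sites, and their p-values are not valid at face value. For consumer outcomes the true size of a nominal 5% test lies between about 14% and 50% as the eligible share goes from a tenth to all, at ICC 0.013 and equal site sizes. With all consumers analysed it runs from 32% at ICC 0.005 to 72% at ICC 0.05. Chart comparisons are at about 16% and staff comparisons at about 6-8%, both at ICC 0.013.

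The sentence should be corrected, but it does not put the primary 24-month inference at risk, so it ranks below the issues that must be resolved before the trial's main result can be trusted. What remains is the risk that supplementary p-values are cited selectively.

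**What to change.** Remove the chi-square and t-tests as tests of intervention effect. Report arm summaries at each time point descriptively, and state that all inference between the arms comes from the models with a site random effect.

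If a simple unadjusted test is wanted, either compare the 14 site means, stratified by state, or run a permutation test over the 1,400 allocations that the state-blocked randomisation allows.

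The cost is a change of wording, with no new data. P-values from the supplementary comparisons will be less favourable than the unadjusted ones; the primary mixed-model results do not change.

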#### Consumer outcomes

##### Community mental health visits

Mental health visits at each agency are reported via the CMHC Service Ticket Form, which is completed by providers after each scheduled appointment or unscheduled visit. Visits are coded as no show, canceled, unscheduled or scheduled.

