##### Medication adherence

Medicaid claims data will be used to measure adherence to psychiatric medications. We will calculate adherence to newly initiated and ongoing use of antidepressants, antipsychotics and mood stabilizers using the medication possession ratio (MPR) [45]. The MPR is a continuous measure of the usable days supplied from all prescriptions in each period divided by the number of days in each period.

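### A Gaussian linear mixed model is stated for every Aim 1 outcome, though several are yes/no, nominal or counts, and length of stay is undefined for consumers never admitted

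*Protocol article*

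**What the plan says.** All of this is in the Methods of the protocol article.

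- **Model.** Under Quantitative Data analysis, differences between arms "will be analyzed using the PROC MIXED statement in SAS statistical software". For Aim 1 the text continues "We will use each outcome as the dependent variable", and "we will use separate mixed linear regression models to determine the impact of the intervention on each of the outcomes at each time point". No logistic, count, two-part or other generalized mixed model is named. Aim 2 carries the same techniques over to patient outcomes.
- **Categorical data.** The same section plans chi-square tests for categorical variables at each time point. These are bivariate, with no covariates and no term for site.
- **Growth analysis.** The focus is the time by treatment interaction, described as quantifying a relative difference in the rate of change.
- **Population and unit.** "All analyses will be done by intent to treat (ITT"), with the consumer as the unit of observation for consumer outcomes.
- **Outcomes.** Hospitalization: "The occurrence of any psychiatric hospitalization, the number of hospitalizations and the length of stay for each will be coded". Service tickets: "Visits are coded as no show, canceled, unscheduled or scheduled". State reporting form: "residence and whether the consumer has been homeless in the past 30 days", together with employment and current legal involvement. Medication adherence is different in kind: "The MPR is a continuous measure of the usable days supplied from all prescriptions".

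**The concern.** PROC MIXED fits a linear model with normal errors and, unless told otherwise, one residual variance. A yes/no outcome has a variance tied to its mean, a count of rare events is skewed and full of zeros, and a four-category visit code has no numerical scale. The article separates categorical from continuous variables for its bivariate tests, then drops the distinction for the models, which are the only adjusted and clustered analyses.

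Three things are at stake: precision on rare outcomes, fitted values below 0 or above 1 once covariates are added, and the meaning of the interaction on which the growth analysis turns.

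Length of stay is a separate matter. It is coded for each hospitalization, so it exists only after an event that follows randomisation and that the intervention may change. The article does not say what value a consumer without an admission receives.

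**Working it through.** The article gives no event rate, stay distribution or effect size, so it has no figure of its own to reproduce here. Inputs from the article: 14 sites, 7 per arm (Randomization); ICC 0.013 and about 8,000 consumers (Participants). The mean is 8,000 / 14 = 571 per site; the number eligible is not stated. Event rates and stays below are assumptions, and the pilot ICC is assumed to apply to consumer outcomes.

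**1. Does the error model fit a yes/no outcome?** Variance is p(1 − p) and skewness is (1 − 2p)/√[p(1 − p)].

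| Risk p | Variance | Skewness |
|---|---|---|
| 5% | 0.0475 | 4.1 |
| 10% | 0.090 | 2.7 |
| 20% | 0.160 | 1.5 |

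Constant-variance normal errors are the wrong description.

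**2. Does that spoil the test?** Take risks of 10% v 5% and n per arm, leaving clustering aside. The pooled variance of the difference is 2 × [(0.090 + 0.0475)/2]/n = 0.1375/n. The unpooled variance is (0.090 + 0.0475)/n = 0.1375/n. With equal arms they are identical, so unequal variances do not by themselves distort the standard error.

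Simulated null data, 14 sites of 571, linear comparison of site means on 12 df:

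- Binary, ICC 0.013, risks 2% to 30%, 4,000 runs: type I error 4.5% to 5.1%. Monte Carlo standard error √(0.05 × 0.95/4,000) = 0.3 points.
- Overdispersed counts, means 0.05 and 0.2 per consumer, 1,000 runs: 4.3% and 4.7%. Monte Carlo standard error √(0.05 × 0.95/1,000) = 0.7 points.

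These runs had equal site sizes and no covariates. They do not cover adjusted growth models with random slopes.

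**3. Do the chi-square tests fill the gap?** Design effect = 1 + (m − 1) × 0.013.

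- m = 75: 1 + 74 × 0.013 = 1.962. Simulated type I error at 10% risk: about 15%.
- m = 571: 1 + 570 × 0.013 = 8.41. Simulated type I error: about 49%.

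They do not.

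**4. Scale of the interaction (assumed figures).** Let baseline risks be 20% and 10%, and let both halve. The risk ratio is 0.5 in each arm, so relative change is equal. The linear model sees −10 and −5 points, an interaction of 5 points. A logit model is close to null but not exactly so: the odds ratios are (0.10/0.90)/(0.20/0.80) = 0.444 and (0.05/0.95)/(0.10/0.90) = 0.474.

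**5. Length of stay if only admitted consumers are compared (assumed figures).** Per 100 control consumers: 5 stays of 4 days and 5 of 20 days give 120 days, 120/10 = 12.0 per stay and 1.20 per consumer. If half the short stays are prevented: 2.5 × 4 + 5 × 20 = 110 days, 110/7.5 = 14.7 per stay and 1.10 per consumer. Stay looks worse while inpatient use falls.

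A second check simulated admission driven by latent severity, correlated 0.5 with log-normal stay, with control risk 5% to 20% and risk ratio 0.9 to 0.5. The intervention changed no one's stay. The admitted-only difference was +0.4 to +2.5 days (about 2% to 15%) against the intervention. Total days per consumer, zeros kept, fell by 8% to 44%. Only 400 to 1,600 of 8,000 consumers (5% to 20%) would contribute a stay.

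**The case against.** **A reader might infer that the standard errors and tests are invalid.** The check does not support that. With sites randomised 7 v 7, a linear comparison that respects clustering holds close to 5%, and a linear model of a yes/no outcome estimates a risk difference, which is a sensible quantity. This stands, within the limits given in step 2 of the working.

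**A reader might also infer that the length-of-stay comparison is not ITT.** The article does not say so. The outcome section describes how stays are coded; it defines no admitted-only population and no stay-per-admission endpoint. The analysis section states ITT with the consumer as unit, and total days with zeros would fit that wording. Bias arises only if consumers without an admission are left out. The direction-reversal example likewise rests on assumed figures.

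**Not every outcome is affected.** The medication possession ratio, the satisfaction, functioning and connectedness scores, and hours worked can reasonably go into a linear model. Nothing in the article makes hospitalization or length of stay the primary outcome. The word relative in the growth analysis may be loose usage for a between-arm difference, but then the scale remains unclear.

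**The detail may be in a fuller document.** That answers how claims become one value per consumer. It does not answer the model form, which the article states for each outcome.

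**Conclusion.** The point holds as a poor choice of stated method, not as an invalid primary test. One Gaussian linear model is prescribed for outcomes that include yes/no, nominal and count variables; nominal codes cannot be used in it as recorded; and the fallback chi-square tests ignore clustering, with type I error of about 15% to 49% under the pilot ICC. The loss from the linear model itself is efficiency, impossible fitted values and an ambiguous interaction scale.

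Length of stay needs a definition covering every eligible consumer. Without one, an admitted-only analysis remains possible and could be biased by the amounts shown, which depend wholly on assumed admission rates, risk ratios and stay distributions. The change is worth making because it is cheap and closes that route.

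**What to change.** - Keep PROC MIXED for scale scores and the medication possession ratio.
- For yes/no outcomes, including a dichotomised visit code such as no-show, use PROC GLIMMIX with a logit link. For hospitalizations, emergency use and visits, use a negative binomial model with a person-time offset. Include site random effects, person effects where measures repeat, and a degrees-of-freedom correction suited to 14 sites.
- State how nominal codes such as residence are recoded before modelling.
- Report marginal risk differences or rate ratios, and name the scale on which time by treatment is judged.
- Replace stay per admission with total psychiatric inpatient days per eligible consumer, zeros included, using a negative binomial or two-part model.
- Treat the chi-square tests as descriptive, or replace them with tests that respect clustering.

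Cost: protocol or SAP wording and modest programming on the same data. Rare events with 14 sites may cause convergence problems, so name a cluster-level linear analysis as the fallback in advance.
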